### Objective 3: economic assessment

#### Design

A cost-benefit assessment will be conducted, as it is particularly well suited for assessing the cost-effectiveness of an intervention [51]. The assessment will compare the costs and consequences of the intervention with the costs and consequences of doing nothing, based on the following time references: the 12 months preceding the start of the intervention and the 12 months following the implementation of all the activities provided for in the action plans. The analysis will take into account the trends observed during the year.

#### Variables

The assessment will be carried out from the standpoint of the institution, by sticking to monetizable costs and benefits only. The direct and indirect costs of the interventions will be identified, the value of them estimated, measured and aggregated to arrive at the total cost [52].

The direct costs will include the costs of the resources associated with developing the intervention: (1) human resources (project manager, workers taking part in workshops, facilitators); (2) physical resources (materials, equipment). The direct costs will also include the costs associated with implementing the intervention. They will vary from one setting to the next depending on the intervention chosen.

The indirect costs will essentially consist of the costs associated with replacing the team members who will be taking part in developing the intervention (workshops) or in action plan activities.

The consequences will be measured on the basis of three parameters: benefits paid for absences from work; costs of replacing employees absent from work; costs of recruiting and integrating replacements.

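### Workshop participants' time and the cost of replacing them are both added into the total cost, so replaced hours are counted twice

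*Protocol article*

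**What the plan says.** All references are to the protocol article, Component 2, Objective 3 (economic assessment), unless noted.

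- **Perspective (Variables):** "The assessment will be carried out from the standpoint of the institution, by sticking to monetizable costs and benefits only".
- **Comparator (Design):** the assessment will "compare the costs and consequences of the intervention with the costs and consequences of doing nothing".
- **Direct costs (Variables):** the development costs include "human resources (project manager, workers taking part in workshops, facilitators", together with materials and equipment. Implementation costs are also direct and will differ between settings.
- **Indirect costs (Variables):** essentially the cost of "replacing the team members who will be taking part in developing the intervention (workshops) or in action plan activities".
- **Total cost (Variables):** direct and indirect costs are summed. No rule assigns an hour to one heading or the other.
- **Consequences (Variables):** three parameters, namely "benefits paid for absences from work; costs of replacing employees absent from work", and, third, the recruitment and integration of replacements. The section does not say whether replacement means the substitute's full pay or only the extra over the absent worker's wage.
- **Data collection:** costs come from a structured form completed by the departments concerned, and consequences come from human resources records.
- **Analysis:** consequences are compared with the previous year, and the result is a cost-benefit ratio.
- **Workshop size (Component 1):** at most 15 participants per institution, with one workshop of 2 h and five of 1 h.

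**The concern.** From the institution's standpoint, and against doing nothing, a cost belongs in the total only if the intervention causes it. A nurse who attends a workshop and is replaced on the ward would have been paid for that hour in any case. What the intervention adds is the substitute. Entering the nurse's time as a direct cost and the substitute as an indirect cost, and summing them, charges the intervention for two hours when it caused one.

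The ratio is the only summary measure named for Objective 3. An inflated total cost makes the interventions look less worthwhile than they are. It would also make the four institutions hard to compare if their departments fill in the form differently, one entering both items and another only one.

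The consequence list raises a related question. If an absent worker's regular wage stops while a benefit is paid, the institution's extra cost on a replaced day is the benefit plus the replacement minus that wage. The list contains no such deduction. Whether one is needed depends on what the replacement item is taken to mean.

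**Working it through.** The article states no cost, benefit or ratio, so there is no economic figure to reproduce. The check uses accounting identities in units of the worker's regular hourly wage.

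**Workshop hours**

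Inputs from Component 1:
- participants: at most 15 per institution
- hours per participant: 2 + 5 × 1 = 7
- ceiling: 15 × 7 = 105 person-hours per institution, or 4 × 105 = 420 over the four

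Assumed, because the article does not give them: share of hours replaced, ρ, from 0 to 1; replacement price, r, from 1.0 to 1.5 regular wages.

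Cost per participant hour:
- as listed: 1 + ρr
- counted once: ρr + (1 − ρ)
- excess: (1 + ρr) − (ρr + 1 − ρ) = ρ

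The excess is ρ × 105 regular wage-hours per institution, whatever r is.

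| ρ | r | As listed | Counted once | Ratio |
|---|---|---|---|---|
| 0 | 1.0 | 1.0 | 1.0 | 1.00 |
| 0.5 | 1.0 | 1.5 | 1.0 | 1.50 |
| 1 | 1.0 | 2.0 | 1.0 | 2.00 |
| 1 | 1.5 | 2.5 | 1.5 | 1.67 |

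With everyone replaced at the regular wage, 210 wage-hours are booked instead of 105.

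In money, at an assumed 30 to 60 dollars per hour, the ceiling is 105 × 30 = 3,150 to 105 × 60 = 6,300 dollars per institution. At 45 dollars per hour (105 × 45 = 4,725) with all hours replaced at r = 1.0, the effect on total cost depends on the other costs, which are also assumed:
- other costs 20,000: (20,000 + 9,450) / (20,000 + 4,725) = 1.19
- other costs 100,000: (100,000 + 9,450) / (100,000 + 4,725) = 1.045

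**Action plan activities**

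The indirect heading also covers replacement for these activities. If participants' time is booked under direct implementation costs as well, the same identity applies. The article gives no activity hours, so no ceiling can be set.

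**Absence days (conditional)**

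Let b be the benefit and r the replacement cost per replaced absent day, in daily wages. If replacement is booked gross and the regular wage stops:
- booked: b + r
- incremental: b + r − 1
- excess: one daily wage for each replaced day avoided

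Comparing with the previous year does not remove the excess, because each avoided day is still valued at b + r. If replacement is already booked as the amount above the wage saved, or if the wage does not stop, the excess is nil. The article gives neither b nor r, nor the share of absent days replaced.

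**The case against.** **The two workshop items may refer to different hours.** Direct cost for participants who are not replaced, and replacement cost for those who are, would be correct accounting. The workshop group also includes doctors, human resources and nursing representatives and a patient partner, and nothing says that all will be replaced. This stands as a limit on size: 105 hours is a ceiling, and if the patient partner is one of the 15 it falls to 14 × 7 = 98 for staff. It does not remove the point, because the article names the same activity under both headings and sums them without stating such a split.

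**The overlap is conservative.** It raises cost and so understates the value of the interventions. That is true, but a biased total is still worth correcting when one sentence does it.

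**A condensed article leaves unit costing to the full protocol.** This carries weight for the absence items, where the article names categories and gives no valuation formula. It carries less for the workshop time, where the duplication lies in the stated list itself.

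**A stronger reading is tempting.** A reader might infer that absence is valued gross, that its benefit is therefore overstated about 1.7 to 2.7 times, and that the cost-benefit ratio is wrong. The article does not support this:
- It never says that replacement is valued gross, and an incremental reading fits its own comparator. Benefits and replacement are both real outlays, so pairing them is not in itself an error.
- The range needs an assumed b of 0.6 to 1.0, an assumed r of 1.0 to 1.5 and every absent day replaced: 2.5 / 1.5 = 1.67 and 1.6 / 0.6 = 2.67. It also leaves out the third parameter, recruitment and integration. Adding that at an assumed 0.5 wage per day gives 3.0 / 2.0 = 1.5 to 2.1 / 1.1 = 1.9.
- Deducting the wage on every absent day would create a new error. On an unreplaced day with b = 0.6 it gives 0.6 + 0 − 1 = −0.4, so absence would appear as a saving.
- It cannot be said that the absence effect outweighs the workshop overlap, because neither the absence hours avoided nor the activity hours are given.

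**Conclusion.** The workshop point holds. Followed as written, the cost list adds a replaced participant's own time to the cost of the replacement, although only the replacement is incremental to doing nothing. The total cost is overstated by the regular wage for each replaced hour: between 0 and 105 person-hours per institution for the workshops, plus an unknown amount for action plan activities if participants' time is booked there too. Its weight in the ratio depends on wages, replacement shares and other costs, none of which the article gives.

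The absence point holds only conditionally. If replacement is booked gross while the regular wage stops, the benefit of avoided absence is overstated, but the document does not allow the amount to be calculated.

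The two effects would act in opposite directions on the ratio, and the net direction is unknown. What is established is a correctable overlap in the cost list and an undefined term in the consequence list, not a wrong ratio.

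**What to change.** In Objective 3, Variables, add a counting rule: *each hour a worker spends in a workshop or an action plan activity enters the total cost once, at the replacement cost if the worker was replaced for that hour, and at the worker's own paid time if not.* Valuing unreplaced time at the wage treats it as work forgone, which matches the article's choice to list participants as a cost.

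As a secondary change, define the replacement parameter: *the cost of replacing an absent employee is the replacement cost in excess of any regular wage that the institution stops paying, applied to replaced days only.* The limit to replaced days avoids the negative cost shown above.

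Put both rules on the structured cost form before the institutions complete it, so that all four apply them alike.

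The cost is small: a replaced or not-replaced entry for participant hours, and regular wage and replacement status for absences, mostly from departments already supplying the data. The design does not change. The ratio may move in either direction, since the first rule can only lower the total cost and the second can only lower or leave unchanged the value of avoided absence.

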#### Data collection

Data on direct and indirect costs will be collected using a structured form that will be filled in by the respondents involved (e.g.: cancer care department, HRD). Data on consequences will be compiled from HRD administrative data.

#### Analysis

The consequences of the intervention will be compared with the previous year. The monetary valuation for these two periods will be done in terms of constant dollars, which will be sufficient to make the two close periods comparable without needing to apply a discount rate. The cost-effectiveness of the intervention will be calculated using the cost-benefit ratio.

### Component 3: analysis of co-construction and implementation process

#### Objectives

The purpose of this component is to (1) describe and assess the approaches used to engage stakeholders in the co-construction and implementation of the interventions; (2) identify the factors that have fostered or impeded the co-construction, implementation and long-term sustainability of the interventions.

#### Design

A longitudinal multiple case study is proposed. The cases will be the cancer care teams at each of the participating institutions.

#### Data collection

Case construction will essentially involve qualitative data collected from a variety of sources: workers in the various job categories, individuals involved in co-construction or implementation, managers (*n* = 12 for each case, to the point of data saturation). The collection methods will be interviews and compiling the relevant documentation. The interviews will be repeated, at two times: three and 12 months after the start of the intervention. The interview guide will cover numerous aspects: resources invested, actors mobilized, implementation methods, facilitating and constraining factors for individuals and teams.

#### Analysis

Once the transcriptions have been coded (Atlas.ti software), the data processing will involve narrative analysis [53] and constant comparative method [54] techniques. The initial aim of the analysis will be to describe the observations for each case. Comparative analysis will then be used to compare the cases and identify similarities and differences. The longitudinal analysis will use narrative investigation approaches to reconstitute the sequence of main events and the links between them [55].

## Discussion

A number of strategies have been used, both in the design of the project and in its rollout and implementation, to ensure its feasibility and long-term sustainability. In the participating institutions, the project has been placed at the top of management committees’ strategic agenda, with commitments to it having been made at the highest level of the cancer care, human resources and nursing departments and by chief executive officers. The project takes a participatory approach that engages all key stakeholders. This ensures that the targeted problems and objectives are consistent with organizational priorities and that the proposed interventions are feasible and broadly accepted. To optimize coordination of project implementation, we will build on the following structure: steering committee, local implementation committee and employee ambassadors. These committees are designed to ensure continuous liaison with permanent stakeholders, which will take over at the end of the project cycle. The make-up of these committees will be adapted on the basis of local characteristics. Implementing the action plans resulting from the workshops will depend in large part on contributions in kind by the institutions and will be consistent with the mission of the human resources departments. Our approach is to serve as a catalyst for the development and implementation of new interventions by providing the support required to strengthen resilience abilities. It will enable cost-effective interventions that maximize the use of internal resources and improve existing processes.

In addition to knowledge production, the project will have direct and indirect benefits for the teams and the institutions, both in the short and long term.

In the short term, the project is expected to have beneficial impacts at three main levels:
*A reduction in the burden associated with mental health problems in interdisciplinary cancer care teams.* Four co-constructed interventions will be rolled out respectively in four institutions, with the objective of not only strengthening team resilience, but also of maintaining team mental health and optimizing work participation. Implementing these interventions will thereby help reduce both the monetary costs (absences from work, lost productivity) and the human burden (lower quality of life) associated with mental health problems.*A strengthening of the abilities of cancer care teams and their organizations*. The empowerment perspective that guides this project means that stakeholders develop the abilities required so that they themselves can create more suitable work environments. The project provides many opportunities to develop these abilities. The proposed co-construction approach gives organizational players a unique learning opportunity to draw up, experiment with and refine solutions to problems in their work environment. The intervention framework that provides guidance for intervention content will serve to build a continuum of three types of abilities that help maintain resilience.*Building a toolbox that could be used by all cancer care teams in Quebec and elsewhere to develop their resilience and revitalize their workplaces*. Beyond the participating institutions, the same approach could be adopted by other teams to develop innovative interventions based on reflective practices. The various outcomes of this study will constitute tools that can be adapted and deployed by other cancer care teams throughout Quebec: work situation analysis tools; methodology of operationalizing the co-construction approach; facilitation tools; communications tools; action plans; intervention implementation tools; assessment tools. The project will be carried out in four institutions whose workplace settings differ in a number of respects: institution’s mission and clienteles, team size, team composition, organization of cancer care services. This kind of variety necessarily increases the range of institutions that could take this project as a basis for designing their own intervention.

Over the longer term, this proposal lays the foundations for a more coordinated, more comprehensive, systemic approach toward occupational health interventions. It will thereby help foster the development of organizational practices and human resources policies that give greater weight to the multidimensional nature of occupational health issues, with respect to both their determinants and their consequences. The adoption and institutionalization of the proposed approach in a growing number of institutions and the long-term sustainability of the resulting interventions will help make lasting improvements in cancer care work environments, with the potential of ensuring greater viability of the workforce in this field. Beyond cancer care, the project will also serve as a springboard to help organizations develop better collaborative and interdisciplinary intervention practices. The lessons learned in cancer care could be extended to other areas facing similar challenges (e.g.: palliative care). Transferability to other areas will be facilitated in particular if human resources departments and nursing departments are involved.

As in other areas of care, patient well-being in cancer treatment is closely linked to the well-being of the professional staff. In addition to its impact on work environments, this project will establish a set of conditions (staff retention and stability, maintaining staff health, work attendance) that will improve the quality of care for cancer patients.

## Data Availability

Although data collected for this study will be stored for up to 7 years, the datasets generated and analyzed will not be available to people outside the research team, due to conditions of the ethical approvals. However, detailed information on the analyses conducted will remain available.

## Abbreviations

CHU: Centre hospitalier universitaire (university hospital center)
CIUSSS: Centre intégré universitaire de santé et de services sociaux (integrated university health and social services centre)
CISSS: Centre intégré de santé et de services sociaux (integrated health and social services centre)
HRD: Human resources department
